### Health economics measures

Data collection for the health economic evaluation will take a patient-level perspective,^60 61^ recording the cost per session of treatment and productivity losses resulting from time off work as a consequence of their mental health difficulties. Data will be collected using the Healthlines Resource Use Questionnaire,^60 61^ which is a measure of the participants' use of healthcare services (including NHS, help at home), occupational productivity (ie, time off work) and cost of transdiagnostic treatment delivery (eg, direct and indirect time spent in service delivery). The Medical Outcomes Study Questionnaire Short Form 36 Health Survey (SF-36),^62^ a generic quality of life questionnaire, will measure overall health and well-being, daily functioning and general life satisfaction across multiple domains. These measures allow calculation of the additional number of quality of life years the treatment will yield. These data will allow preliminary estimates of the potential cost utility of the transdiagnostic intervention and also of the feasibility of acquiring these data within the trial protocol.

## Methodological aspects

### Power analysis and sample size

Although a standard power calculation based on detecting treatment effects is the conventional approach to determining sample sizes for trials, the main aim of the current trial is to elucidate feasibility for a larger later-stage evaluation. We therefore sought at this stage only to provide a point estimate of the effect of *SHM* to inform a power calculation for this putative fully powered later-phase evaluation. Our previous experience with such early phase trial platforms indicates that 50 patients will provide sufficient numbers and diagnostic diversity to evaluate feasibility, acceptability and procedural uncertainty for *SHM* and a plausible test of recruitment protocols. This will give 40 patients (20 per arm) at 3-month post-treatment follow-up, assuming 20% attrition. This will provide a reasonable range of point estimates of effect on our set of candidate outcome measures sufficient to guide later phase trial work.

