### Participants and recruitment

The proposed feasibility study will seek to recruit 50 people aged 18 years and above with a primary diagnosis of a unipolar mood, anxiety, obsessive-compulsive, or trauma-related and stressor-related disorder (CMHPs) with at least one additional comorbid diagnosis according to the Diagnostic and Statistical Manual of Mental Disorders, Fifth Edition (DSM-5).^29^ Participants will be randomly allocated to one of two groups: (1) *SHM* or (2) TAU. Diagnosis of CMHPs will be determined by trained research staff using the Structured Clinical Interview for DSM-5 (SCID-5).^30^ To be eligible, participants will also need to score >10 on either the Patient Health Questionnaire (PHQ-9) or the Generalised Anxiety Disorder Questionnaire (GAD-7; see study measures below). Exclusion criteria are current/past psychosis or bipolar disorder, current diagnosis of alcohol or substance use disorder (all assessed via SCID-5^30^), organic brain damage, complex trauma history or recurrent self-injury requiring specialist services, or current suicidality that warrants immediate clinical attention and constitutes a current risk of harm to the individual (all assessed via participant report and the clinical care team). Participants may be engaged with the multidisciplinary clinical care team, but those randomised to *SHM* will not be receiving other psychological services while participating in the trial. All other services (eg, medication review with psychiatrist or general practitioner, occupational therapy, social support services) may be continued, and there are no medication exclusions.

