### Dissemination policy

There are no publication restrictions and findings will be disseminated broadly to participants, healthcare professionals, the public and other relevant groups. Academic outputs will take the form of peer-reviewed empirical journal articles, commentary pieces and conference presentations. Clinical outputs will be prioritised by the research team in order to maximise the impact of the findings with practitioners and commissioners. Outputs will comprise clinical conferences, workshops, service user groups and a study website that will make the intervention materials and related measures generally available. We will send all participants a report describing the findings and their implications. We will also make participants aware of the study website. We anticipate that trial findings will inform future revisions of clinical guidelines for numerous forms of mood, anxiety and stress disorders, and the development of guidelines for comorbid conditions. Anonymised data from the trial will be made publicly available on an open access database.

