## Discussion

A significant proportion of the cost of CMHPs is generated by adults suffering from complex and comorbid depression, stress and anxiety, where treatment non-response, cross-sector service use across health, social care and housing, and loss of productivity are greatest. Providing effective interventions for these mental health problems therefore has the potential to reduce both long-term treatment costs as well as prevent large productivity losses. At present, most psychological interventions focus on specific diagnoses and many treatment manuals take a ‘one-size-fits-all’ approach. Current evidence-based interventions only achieve clinical recovery for 40%–70% of patients, with people suffering complex comorbid conditions faring significantly worse. This randomised controlled feasibility trial aims to pave the way for a scaled-up efficacy trial of a new transdiagnostic modular treatment for all CMHPs—*SHM—*that enables the flexible delivery of evidence-based techniques. This treatment approach may improve the effectiveness and dissemination of evidence-based interventions for the many individuals for whom diagnosis-specific treatments leave significant difficulties unaddressed. The results from this trial will provide a range of estimates of effect sizes that can be used to power a later-stage trial of treatment efficacy, to refine the treatment protocol and to inform future evaluation of the mechanisms underlying any treatment effects. If effective, *SHM* has the potential to improve outcome for those with complex presentations, through offering a cost-effective treatment option to reduce chronic, transdiagnostic psychological difficulties.

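### The effect estimate from 20 patients per arm is offered as the basis for powering the later trial, but its 95% CI half-width is about 0.46 to 0.64 SD

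*Protocol article*

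**What the plan says.** In the protocol article, Power analysis and sample size declines a conventional power calculation because feasibility is the main aim. It then says that a point estimate of the effect is sought "to inform a power calculation for this putative fully powered later-phase evaluation". The justification for the number of patients is experience: "Our previous experience with such early phase trial platforms indicates that 50 patients will provide sufficient numbers and diagnostic diversity", which that sentence goes on to tie to feasibility, acceptability, procedural uncertainty and a test of recruitment. The yield is stated as "This will give 40 patients (20 per arm) at 3-month post-treatment follow-up, assuming 20% attrition". The section ends with the sufficiency statement: "This will provide a reasonable range of point estimates of effect on our set of candidate outcome measures sufficient to guide later phase trial work".

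The Discussion returns to this use and says that the results will supply "a range of estimates of effect sizes that can be used to power a later-stage trial of treatment efficacy".

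Neither section gives an expected interval width, a precision target or a minimally important difference. The Statistical analysis plan section allows for baseline covariates as appropriate and for multiple imputation of missing data, both of which affect precision.

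**The concern.** Two different jobs are asked of the same 50 patients. For the first, feasibility, the article gives a reason for the number. For the second, an effect estimate good enough to help size the next trial, it gives none, yet it calls the result sufficient.

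A required sample size varies with the inverse square of the assumed effect, so an error in the estimate is magnified when it is turned into a number of patients. An overestimate gives a later trial that is too small. An estimate at or below zero gives no usable sample size for showing a benefit. The comparator adds to the difficulty: under Treatment-as-usual, controls receive active specialist psychological therapy, so a small true difference is plausible, and that is where an imprecise estimate helps least.

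**Working it through.** **The plan's own figure.** 50 × (1 − 0.20) = 40, or 20 per arm. This reproduces exactly. The article gives no alpha, power, effect size or SD for the effect estimate, so there is nothing further to reproduce.

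**Inputs.**
- n = 20 per arm at 3 months (Power analysis and sample size).
- Standardised scale, SD = 1; two-sided 95% interval (assumptions).
- Baseline-outcome correlation r: not stated. Assumed range 0 (no adjustment) to 0.7, because baseline covariates are planned.
- True effect 0.4 SD and 90% power for the later trial: illustrative assumptions.

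**Precision.** SE = √[(2/n)(1 − r²)]; half-width = t × SE, with 38 degrees of freedom unadjusted and 37 adjusted.

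| r | SE | t | 95% half-width (SD) |
|---|---|---|---|
| 0 | √0.1 = 0.316 | 2.024 | 0.640 |
| 0.5 | √(0.1 × 0.75) = 0.274 | 2.026 | 0.555 |
| 0.7 | √(0.1 × 0.51) = 0.226 | 2.026 | 0.458 |

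As a most favourable case, suppose imputation recovered the full information from all 25 per arm and r = 0.7. Then SE = √(0.08 × 0.51) = 0.202, t = 2.012, and the half-width is 0.41.

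**Wrong sign.** With a true effect of 0.4 SD, P(estimate < 0) = Φ(−0.4/SE):
- r = 0: Φ(−1.26) = 10%
- r = 0.5: Φ(−1.46) = 7%
- r = 0.7: Φ(−1.77) = 4%

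**Later trial sized on the estimate.** For 90% power, n per arm = 2(1.96 + 1.2816)²/est². Its true power at 0.4 SD is Φ(0.4 × 3.2416/est − 1.96). If the later trial also adjusts for baseline in both planning and analysis, the factor (1 − r²) cancels here. True power falls to 50% when est = 0.4 × 3.2416/1.96 = 0.662. So P(true power < 50%) = P(estimate > 0.662):
- r = 0: (0.662 − 0.4)/0.316 = 0.83, giving 20%
- r = 0.5: 0.262/0.274 = 0.96, giving 17%
- r = 0.7: 0.262/0.226 = 1.16, giving 12%

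In patients: at the true 0.4 SD the later trial needs 2 × 3.2416²/0.4² = 131.3, so 132 per arm. An estimate of 0.662 would lead to 2 × 3.2416²/0.662² = 47.96, so 48 per arm.

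**The case against.** The best defence is that this is openly a feasibility trial, that it declines a power calculation for that reason, and that the strongest wording is softer than it may look. The sufficiency sentence speaks of guiding later work, and the sentence before it of informing a power calculation. Only the Discussion says that the estimates can be used to power a trial. A reader who joins these might infer that the protocol calls the estimate sufficient to power the next trial; no single sentence says so. That limits the charge but does not answer it, because both sections still give the effect estimate a use that its precision does not support.

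It is also fair that 0.64 SD is the unadjusted figure and that baseline covariates are planned, so a range is the right way to state the precision. Another fair point is that sizing a trial on any point estimate often leaves it below 80% power. In the example above, unadjusted, this happens in 42% of repeats with 20 per arm and still in 26% with 200. The share below 50% is the better measure of what 20 per arm costs.

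Several stronger readings are not supported:
- A reader might infer from the mention of candidate measures that the later primary outcome will be picked by its observed effect, with upward bias. The document states no such rule, and it names the three co-primary outcomes in advance.
- A reader might infer that a chance null result would end the programme. No stop rule tied to efficacy is given.
- The absence of a commitment to report intervals is no defect in a condensed article whose analysis plan is not shown.
- The hope in Dissemination policy of informing guidelines is not a claim about sample size.

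**Conclusion.** The concern holds in limited form. The protocol presents the observed effect from 20 per arm as an input to the later power calculation and as sufficient guidance. Its 95% interval would extend about 0.46 to 0.64 SD either side, for an assumed correlation from 0.7 down to 0, and 0.41 in the most favourable case examined. An interval that wide around a moderate effect runs from near or below zero to a large effect. The wrong-sign and low-power figures further assume a true effect of 0.4 SD and a later trial sized for 90% power directly on the point estimate. The document does not prescribe that rule, so they illustrate the risk of the stated use and do not forecast what the team will do. Fifty patients are not faulted for the feasibility aims. The point should be corrected, but it does not threaten the trial's main purpose.

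**What to change.** In Power analysis and sample size, add the expected precision: with 20 per arm, a 95% CI half-width of about 0.46 to 0.64 SD for an assumed baseline-outcome correlation between 0.7 and 0. Replace the sufficiency sentence there, and the matching sentence in the Discussion, with text such as:

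*This trial will supply the outcome SD, the baseline/follow-up correlation, and the retention and recruitment rates for the later sample size calculation. The later trial's target difference will be set from a minimally important difference. The observed effect, with its 95% confidence interval, will be used only to check whether it is compatible with that difference.*

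The change is to wording only and needs no more patients, visits or measures. Its cost is that the stated value of the efficacy estimate becomes less favourable, and that a minimally important difference must be justified before the later trial is sized.

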### Data collection and confidentiality

Outcome data for all participants who are randomised will be collected via face-to-face interviews and written questionnaires at baseline, post-treatment and 3-month follow-up. To maintain confidentiality, all participants will be given a trial number so that personally identifying information is not linked to assessment or trial information. All data (including personally identifiable information) will be stored on secure UK NHS databases, secure University of Cambridge servers and within locked filing cabinets under the management of the trial coordinator. Access will be limited to the immediate clinical research team.

### Blinding

Outcome assessments will be conducted by independent raters who have no therapeutic relationship with the patients and are blind to treatment condition. Double blinding of patients and therapists is not possible due to the nature of the trial (ie, a psychological intervention). Unblinding will not be necessary because participants and therapists are not blinded to intervention allocation.

### Statistical analysis plan

Initial analyses of the outcomes will be conducted by the trial statistician, blind to trial condition, following Consolidated Standards of Reporting Trials (CONSORT) standards (see online supplementary figure file 2). There are no planned interim analyses. Initial analyses will be conducted on an intention-to-treat basis, with subsequent analyses being per protocol. Mixed-model analyses of variance will be used to compare groups on outcomes at the three assessment points—baseline, postintervention and 3-month follow-up. Baseline levels on relevant measures will be included as covariates, as appropriate. Both intent-to-treat and per-protocol exploratory analyses will be conducted with our range of outcome measures following CONSORT standards. Multiple imputation will be used to account for missing data. Intent-to-treat analysis will also be used for those lost to attrition. Exploratory moderation and mediation analyses to examine process variables will be conducted using the MacArthur approach.^63^ For the health economic data, costs associated with service use will be calculated by attaching a unit cost to each instance of use, and data will be combined with QALYs^62^ derived from the SF-36 to arrive at a preliminary estimate of the cost utility of the transdiagnostic intervention.

10.1136/bmjopen-2018-024546.supp2Supplementary data

### Monitoring and data management

The trial will take place at NHS sites and a research unit in the East of England. A Trial Management Group (TMG), will meet one to two times a year to: manage the protocol; monitor recruitment in relation to targets; deal with any adverse events; and coordinate the different stages of the project. The TMG consists of research clinical psychologists and assistant psychologists, a psychiatrist, a health economist, clinical psychology researchers, the trial statistician, a nurse practitioner and a service user representative. Day-to-day project management will be the responsibility of a smaller trial team, meeting fortnightly to deal with administrative issues, troubleshooting and recruitment flow. Clinical supervision will take place fortnightly. As this is a phase I/II trial, a data management committee was deemed unnecessary, and as such the trial team are responsible for monitoring and data management. Data will be monitored for completeness and consistency using spot checks and plausibility checks carried out by the trial statistician. The trial lead, trial coordinator and statistician will have full access to the final trial data set. The study data will be reported in line with the current CONSORT recommendations.

### Patient and public involvement

Most broadly, the driving force behind the development of *SHM* has been feedback from many hundreds of service users in clinical settings, specifically related to the suitability of treatments for complex and comorbid CMHPs. A Lived Experience Group comprising service users and carers hosted by the Cambridge Centre for Affective Disorders discussed the details of the current study at its meeting on 12 November 2013. This group provided useful feedback to the research team in terms of the materials for service users (eg, consent forms), the clinical setting for the intervention, and optimal forms of Patient and Public Involvement (PPI) involvement (specifically, the use of service user researchers to conduct qualitative interviews with service users). Further, we received service user input on the content of the draft treatment modules, and a part of this feasibility trial will be receiving feedback from participants on their experience of participating in the trial and using the manuals. We will send all participants a report describing the findings and their implications. We will also make participants aware of the study website. There will be a number of roles following completion of recruitment including the refinement and revision of the treatment manual along with involvement in the academic output preparation.

## Ethics and dissemination

### Ethical approval and protocol amendments

The study will be conducted within appropriate UK MRC, NHS and professional ethical guidelines, ensuring that Good Clinical Practice procedures are adhered to at all times. Protocol amendments will be circulated to the ethics committee, and trial team, and published in the online registration of the trial, and in the trial paper.

### Safety aspects

Adverse events are managed in line with UK Medical Research Council (MRC) protocols and, in the unlikely case of an adverse event, will be documented appropriately. Precautions have been taken to reduce the likelihood of adverse events occurring; for example, patients who are acutely suicidal or at high risk of harm do not meet study inclusion criteria. The interventions are delivered by therapists experienced in the management of risk and in the treatment of psychological disorders. In the case of any adverse events as a result of the intervention that would interfere with participation, participation in the trial will be discontinued. Regular team meetings will be conducted to monitor any difficulties patients may be having and ways of best dealing with these difficulties. Serious adverse events will be reported to the ethics committee. The trial is underwritten by the University of Cambridge in the case that any individual suffers harm or requires post-trial care. Any adverse events will be reported in the trial paper.

### Dissemination policy

There are no publication restrictions and findings will be disseminated broadly to participants, healthcare professionals, the public and other relevant groups. Academic outputs will take the form of peer-reviewed empirical journal articles, commentary pieces and conference presentations. Clinical outputs will be prioritised by the research team in order to maximise the impact of the findings with practitioners and commissioners. Outputs will comprise clinical conferences, workshops, service user groups and a study website that will make the intervention materials and related measures generally available. We will send all participants a report describing the findings and their implications. We will also make participants aware of the study website. We anticipate that trial findings will inform future revisions of clinical guidelines for numerous forms of mood, anxiety and stress disorders, and the development of guidelines for comorbid conditions. Anonymised data from the trial will be made publicly available on an open access database.

## Discussion

A significant proportion of the cost of CMHPs is generated by adults suffering from complex and comorbid depression, stress and anxiety, where treatment non-response, cross-sector service use across health, social care and housing, and loss of productivity are greatest. Providing effective interventions for these mental health problems therefore has the potential to reduce both long-term treatment costs as well as prevent large productivity losses. At present, most psychological interventions focus on specific diagnoses and many treatment manuals take a ‘one-size-fits-all’ approach. Current evidence-based interventions only achieve clinical recovery for 40%–70% of patients, with people suffering complex comorbid conditions faring significantly worse. This randomised controlled feasibility trial aims to pave the way for a scaled-up efficacy trial of a new transdiagnostic modular treatment for all CMHPs—*SHM—*that enables the flexible delivery of evidence-based techniques. This treatment approach may improve the effectiveness and dissemination of evidence-based interventions for the many individuals for whom diagnosis-specific treatments leave significant difficulties unaddressed. The results from this trial will provide a range of estimates of effect sizes that can be used to power a later-stage trial of treatment efficacy, to refine the treatment protocol and to inform future evaluation of the mechanisms underlying any treatment effects. If effective, *SHM* has the potential to improve outcome for those with complex presentations, through offering a cost-effective treatment option to reduce chronic, transdiagnostic psychological difficulties.

### Trial status

This trial was registered at clinicaltrials.gov on 4 May 2017 (NCT03143634). This article was submitted on 31 May 2018. To date, 15 participants have met eligibility criteria for the study and have been randomised to a condition. The trial opened on 31 July 2017, and data collection aims to be completed by September 2019.
